**1- Summary**

Conventional hemodialysis requires systemic transient anticoagulation due to the activation of coagulation by contact between the patient's blood and the extracorporeal circuit. This anticoagulation, which uses heparin - fractionated or not – is however contra-indicated in patients with a high risk of bleeding. In this relatively common situation ( 10% of cases ), many procedures help perform hemodialysis without systemic anticoagulation, but no prospective study compare them. The reference method (" rinses " of the dialysis circuit with saline) is logistically cumbersome and subject to a relatively high failure rate. Two methods are emerging increasing use of : the continuous dilution of the dialysis circuit, and the exclusive anticoagulation the dialysis membrane by prior adsorption of heparin on a membrane having a treated non electronegative surface (NEPHRAL ST 400).

The single-center prospective randomized open controlled trial aims to compare " rinses ", " dilution " and " heparin adsorbed " in patients with a high risk of bleeding. The criteria will be clotting of the dialysis circuit (primary endpoint) and the efficacy and safety of dialysis ( secondary endpoints). This comparison will be made on the basis of statistics of randomized cross-over in unique individuals (" N- of- 1 trial ") series. We plan the inclusion of 78 different patients and implementation of 1050 dialysis without systemic heparinization.

We hope to show that, compared to " rinse " the " dilution " the " heparin adsorbed " technique reduces the frequency of coagulation circuit 30 and 50 %, respectively (primary endpoint) . We also hope to demonstrate that heparin adsorption allows ( i) better preservation of the porosity of the dialysis membranes, maintaining throughout the session a satisfactory removal of uremic waste, (ii) by limiting the use of fluids, helps to reach more often at the end of the session the dry weight of the patient and / or are to better clinically tolerate the dialysis sessions (secondary endpoints).

**2- Introduction**

Patients with end stage renal disease undergo 3 dialysis sessions per week (4 hours per session). Part of their blood (300 ml/minute) is derived by an extraorporeal circuit, and is dialysed in contact with an artificial membrane.

Despite numerous technological, a significant bioincompatibility persists between the blood and the dialysis membrane, which is responsible for complement and coagulation activation (Bartels, Schoorl et al. 2000) (Martin-Malo, Velasco et al. 1993). To avoid coagulation of the dialysis circuit, low molecular weight heparin (LMWH) are used (single bolus when the dialysis session starts) (Camici, Evangelisti et al. 1997). LMWH have supplanted continuous heparin infusions because their use is simpler and their efficiency is comparable (Nurmohamed, ten Cate et al. 1991; Weitz 1997). LMWH provide an excellent extraorporeal circuit anticoagulation, but also induce an efficient systemic anticoagulation of the patient that lasts about 12 heures (Bouffard, Delafosse et al. 1989). Their use is thus at risk, and may be contra-indicated (temporarily or definitively) in case of high bleeding risk.

In such circumstances, several dialysis techniques may avoid systemic anticoagulation (Caruana, Raja et al. 1987; Canivet, Wuillai et al. 2003):

- **Regional anticoagulation**
  - heparin/protamin : heparin is infused continuously in the arterial line of the circuit, while protamin, also infused continuously, neutralises it in the veinous line. Precise adjustment allowing a sufficient anticoagulation in the circuit without systemic anticoagulation is tricky to obtain : 35% of circuit clotting and 25 % of bleeding complications during the dialysis sessions have been reported (Hampers, Balufox et al. 1966) (Lindholm and Murray 1964) (Swartz and Port 1979) (Swartz 1981). This technique is no longer in use.
  - citrate/calcium : anticoagulation results form calcium chelation in the extracorporeal circuit by the sodium citrate continuously infused in the arterial line; the dialysate contains not calcium, and no magnesium (that may block the effects of citrate), but those are reinjected by continuous infusion at the end of the circuit (Pinnick, Wiegmann et al. 1983). This technique must be adapted to patient’s clotting tests and calcemia. Its efficiency is demonstrated, but it is complex, requires a specific dialysate, confers risks of dyscalcemia, metabolic alcalosis, hypernatremia, hyperammoniemia, and is frequently poorly tolerated (nausea, paresthesia, cramps, hypotension) in case of citrate overload (Flanigan, Von Brecht et al. 1987; Kelleher and Schulman 1987; Janssen, Huijgens et al. 1993; Apsner, Buchmayer et al. 2001).
  - AN 69 ST: recently described, this dialysis membrane made of polyacrylonitrile with modified surface (relative disparition of electronegative charges) can adsorb heparin. It is therefore possible to rince the circuit with heparinized saline, and to start the dialysis sessions without adding any anticoagulant, the heparin bound to the membrane playing a local role. Partial or massive clotting were observed in only 10 % of the sessions, in various studies (Delawari, Renaux et al. 2001; Lavaud, Canivet et al. 2002; Lavaud, Canivet et al. 2003) (Tielemans, Neyens et al. 2001).
- **Hémodialysis without anticoagulation**.
  - "discontinuous rinses" iterative rinses dialysis circuit with isotonic saline (from 50 to 300 ml every 15-30 min), have reduced the frequency of coagulation of the circuit to 30%. Some teams added to rinse prophylactic change of the membrane and dialysis circuit during the session (Preuschof, Keller et al. 1988). It is currently the gold standard hemodialysis when systemic anticoagulation is contra-indicated. Its implementation, however, requires substantial nursing work, and involves a nurse per patient (versus a nurse for four patients) throughout the session.
  - "predilution". Many teams use in practice a technique in which a flushing of the dialysis circuit is continuous (infusion of 4 cc of saline per minute in the arterial line). This technique is simple to implement, has never been validated as renal replacement without anticoagulation technique. The risk of clotting system is anticipated to 20%.

***Justification of research***

The main risks associated with the absence of systemic anticoagulation during a dialysis session are:

o complete extracorporeal circuit clotting, causing a blood loss of 300 ml. Iterative spoliation are often responsible for anemia requiring transfusions.

o reduction in the efficiency of dialysis, either by shortening the duration of the session (coagulation) or by micro-sealing of the dialysis membrane (clots invisible to the naked eye). The decrease in efficiency results in insufficient removal of uremic toxins (eg urea) and incomplete salt depletion (dry weight of the patient not reached).

Currently in most dialysis centers, including ours, three hemodialysis techniques without systemic anticoagulation mentioned above are used:

o " rinses" of the circuit with normal saline.

o " predilution " by continuous flushing of the circuit with isotonic saline.

o the use of AN69 ST membrane with adsorbed heparin.

There is at present no studies comparing different techniques of dialysis without systemic anticoagulation. In practice, the choice of which technique to use is primarily based on any rational standard and is left open to the discretion of the physician. It is very common to see in later sessions for the same patient, a strange alternation between different hemodialysis without anticoagulation techniques. These changes sometimes take prescriptions habits or preferences of physicians and dialysis nurses, the more often they are the waning of an accident clotting system. For example, a patient treated with " discontinuous rinses " at its nth session may, in case of clotting, have at the next dialysis session a " dilution " or an "adsorbed heparin" protocol.

*Expected Results and prospects*

In this study we want to compare, on the basis of test series randomized cross-over in unique individuals, three techniques in patients who have a contra-indication to systemic anticoagulation and / or a high risk of bleeding.

Based on retrospective observations conducted in our center last year, we hope to show that, compared to "rinses" (as a reference), the techniques of "dilution "and "adsorbed heparin " reduce the frequency of coagulation circuit 30 and 50%, respectively (primary endpoint).

We also hope to demonstrate that the technique of "adsorbed heparin" ( i) better preserves the porosity of the dialysis membranes, maintains throughout the session a satisfactory removal of uremic waste ( Romao , Fadil et al. 1997), (ii) avoids the intake and ultrafiltration liquid rinse or dilution, helps to reach more often at the end of the session the dry weight of the patient and / or are better tolerated clinically (secondary endpoints).

Dilution and adsorbed heparin are used by a small but growing number of nephrologists during hemodialysis sessions without LMWH. The results of the first prospective trial in the field would rigorously validate their effectiveness, and promote their recognition and distribution within the nephrology community. Implementation throughout the course of these two dialysis techniques without systemic heparinization would theoretically have several advantages (our study did not seek to assess), such as reduced transfusion requirements or erythropoietin, or the reduction of nursing work .

In daily practice, the results of this study will be of great use for the whole community : the superiority of the dilution over the rinse could be generalized to all types of dialysis membranes, while the technique of adsorbed heparin would be exploited by the centers using AN69 ST membrane, which cost is quite high.

**3- Objectives**

**Hypotheses tested**

The technique of " discontinuous rinsing " is currently the gold standard but has a significant cost (equipment and nursing time). We would like to validate the technique of "dilution" under the assumption that it will reduce the percentage of clotting system by 30% compared to the " discontinuous rinses."

The " adsorbed heparin technique " using the AN69 ST membrane is a technological breakthrough and we hope to show that the percentage of clotting decreases by 50% compared to the "discontinuous rinses".

**Primary objective**

The objective of this research project is to compare the dialysis techniques (discontinuous rinses, dilution, adsorbed heparin) in patients with temporary or definitive contra-indication to heparin during their dialysis session, on the risk of complete coagulation of the dialysis circuit.

**Secondary objectives**

The secondary objectives are to compare the dialysis techniques (discontinuous rinses, dilution, adsorbed heparin) in patients with temporary or definitive contra-indication to heparin in terms of efficacy and safety the dialysis session.

**4- Experimental plan**

***Choice of the experimental plan and justification***

It is a single-center, randomized, open-type N-of-1 trial (cross-over test series randomized in unique individuals). This is an open study since the techniques cannot be blinded ; however the endpoint chosen is objective (clotting or non-clotting of the dialysis circuit), and not amenable to interpretation. Moreover, the patient is not necessary blinded because this should not influence the response. The choice of N of 1 trial is justified because it is important to choose the best technique according to the patient, and the experimental design can provide an individual response and assess the repeatability of the response by the same technique in the same patient. This experimental design is made possible due to the completion of three dialysis sessions per week chronically ineffective a dialysis session to the next session with a rapid assessment (the same day as the dialysis session) of the test main judgment and fact will be selected patients with contra-indication for LMWH for at least 3 consecutive dialysis sessions without heparin. In addition, this experimental design allows techniques comparison across treatment groups.

The unit of randomization will be patient and will be made according to the following scheme:

- A = discontinuous rinses, B = dilution and C = adsorbed heparin
- The 6 possibles sequences of treatments are:
  - ABC
  - ACB
  - BAC
  - BCA
  - CAB
  - CBA

The patient will be randomized into one of six arms and make sure to have a number of patients included multiple of 6 (see calculation of the number of subjects required). Randomization will be by random blocks of varying size. The order of the types of sessions vary all three triplets for the same patient if the dialysis without heparin must be repeated beyond the first triplets. As a patient may contribute to several sequences, the patient will be considered as a cluster randomization.

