**5- Design and conduct of research**

***Follow-up***

Each dialysis session includes a medical examination and a nurse monitoring. The information session is recorded in the case report form, some data are automatically transmitted by the generator to the dialysis Sined Medware ® software and recorded in the secure medical file of the patient. The estimated dialysability urea by the generator induces no extra cost.

Information contained in the protocol specification

At the beginning of the session

• weight, blood pressure, heart rate

• since the last session : weight gain and symptoms occurred

Monitoring of the dialysis session

• Continuous (Sined Medware ® Software generator Hospal Integra ®: blood flow, venous pressure, ultrafiltration rate, urea dialysance)

• every 30 ': blood pressure, heart rate.

• incidents during the session: clotting of the circuit (partial / full), clinical symptoms.

At the end of the session: session duration, weight, total urea dialysance

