**7- Endpoints**

***Main criterion***

Need to suspend the session for clotting of the dialysis circuit, because of either :

o complete coagulation of the circuit

o partial coagulation of the circuit (a clot is found in the lines or the bubble trap *)

o increased venous pressure (PV) of the circuit more than 50% beyond its initial value

* Note: the opacity of the fibers of the membrane NEPHRAL 400 ST makes it impossible the assessment of a partial internal filter clotting.

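### The endpoint used to justify the open design is partly a judgement by unblinded staff, and visible clots may be found more readily under rinses

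*Protocol*

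**What the plan says.** Section 4 of the protocol (Choice of the experimental plan and justification) states: "This is an open study since the techniques cannot be blinded". It then offers as reassurance that "the endpoint chosen is objective (clotting or non-clotting of the dialysis circuit), and not amenable to interpretation".

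Section 7 (Main criterion) defines the event as "Need to suspend the session for clotting of the dialysis circuit", for any of three reasons:

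- complete coagulation;
- "partial coagulation of the circuit (a clot is found in the lines or the bubble trap";
- "increased venous pressure (PV) of the circuit more than 50% beyond its initial value".

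A note there adds that partial clotting inside the filter cannot be assessed, because the fibres are opaque.

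Section 5 (Follow-up) lists monitoring for every session. The generator records venous pressure continuously, and blood pressure and heart rate are taken every 30 minutes. Clotting is noted among "incidents during the session: clotting of the circuit (partial / full), clinical symptoms", with no timed check.

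The Introduction says of discontinuous rinses that the technique "involves a nurse per patient (versus a nurse for four patients) throughout the session". Section 6 has the rinse injected on the arterial line every 30 minutes. The primary objective in section 3 names complete coagulation only.

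**The concern.** The open design rests on a property that the endpoint does not fully have. Whether a session needs to be suspended is a decision, and the people deciding know which technique is running. The partial-clot limb adds a visual finding with no grade, no set time to look and no named assessor.

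A difference in attention between techniques could therefore turn into a difference in recorded failures. If closer nursing under rinses leads to more visible clots being found, the recorded rate under A rises relative to B and C. That is the direction of the trial's hypotheses. Randomised order and the crossover do not remove such a bias, because it travels with the technique. Recorded failures also feed into later allocation through the three-consecutive-failures rule in section 8. A positive result could be challenged on this ground.

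**Working it through.** **Setting the texts side by side**

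- Complete coagulation is hard to miss. The pressure limb has a numerical threshold and a machine record behind it. These two limbs are largely protected.
- The seen-clot limb is not protected. It depends on who looks, when, and what they count.
- All three limbs pass through the need to suspend, which is a staff decision.

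So the claim in section 4 fits part of the endpoint in section 7, not all of it.

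**Reproducing the plan's own figure**

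Inputs from section 8: clotting 30% (A), 20% (B), 10% (C); alpha 5%; power 80%. Sidedness is not stated there, but two-sided reproduces the figures. With independent paired responses:

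- A vs B: s = 0.30 × 0.80 = 0.24, t = 0.70 × 0.20 = 0.14, π = s + t = 0.38, ψ = s/t = 1.714.
- n = [z(1−α/2)(ψ+1) + z(power)·√((ψ+1)² − (ψ−1)²π)]² / [(ψ−1)²π] = (5.320 + 2.254)² / 0.1939 = 295.9, so 296 pairs. The protocol states 294. Its rounded ψ of 1.7 would give 305.
- A vs C: π = 0.34, ψ = 3.857, n = 64.3, so 65 pairs, as stated.
- Power at 294 pairs for A vs B: 79.7%.

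The sample size is reproduced and is not in question here.

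**Illustrating the detection effect (assumed inputs)**

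The documents give neither the share f of failures that rest only on a seen clot nor the fraction m of those missed on B. Assume true failure of 30% on both techniques and all failures found on A. Then:

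- recorded rate on B = 30% × (1 − f·m);
- with d = s − t, P(reject) = Φ[(d√N − 1.960√π)/√(π − d²)] + Φ[(−d√N − 1.960√π)/√(π − d²)].

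For f = 0.50 and m = 0.20, the recorded rate on B is 27%, s = 0.30 × 0.73 = 0.219, t = 0.70 × 0.27 = 0.189, π = 0.408 and d = 0.030. At N = 294 the first term is Φ[(0.514 − 1.252)/0.638] = Φ(−1.156) = 0.124. The second is Φ(−2.77) = 0.003. The total is 0.127.

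The range, at 294 pairs (882/3) and 350 pairs (1050/3):

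| f | m | Recorded on B | 294 pairs | 350 pairs |
|---|---|---|---|---|
| 0.25 | 0.10 | 29.25% | 5.5% | 5.5% |
| 0.25 | 0.20 | 28.5% | 6.8% | 7.2% |
| 0.50 | 0.20 | 27.0% | 12.7% | 14.2% |
| 0.50 | 0.50 | 22.5% | 54.0% | 61.4% |
| 0.75 | 0.50 | 18.75% | 88.7% | 93.4% |

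**What it would take to produce the planned effects by detection alone**

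- A vs B: f·m = (30 − 20)/30 = 0.33. With f = 0.50 this means missing 0.33/0.50, about 67% of visible clots on B.
- A vs C: f·m = (30 − 10)/30 = 0.67, which cannot be reached with f = 0.50.

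The calculation uses the paired test of the sample-size section, not the marginal or subject-specific models planned for the main analysis, and it ignores clustering.

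**The case against.** The strongest reply is that unequal inspection is nowhere documented. The one-to-one ratio stands in the Introduction and describes rinsing as generally practised. Sections 5 and 6 set no staffing for trial sessions. Follow-up schedules blood pressure and heart rate every 30 minutes in all three techniques, which is the same interval as the rinses, and it lists partial and full clotting as a recorded incident without distinction by technique. A nurse is therefore due at the bedside at least that often under B and C too. This stands. A reader might infer that clots are in fact looked for harder under A, but the documents support only that they may be detected more readily.

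A reader might also apply under-detection to every failure. With 80% or 70% of all failures found on B, the same formula at 350 pairs gives false-positive rates of 43% or 78%. That reading is too strong, because it supposes that complete clotting and machine-recorded pressure rises are missed as often as a small visible clot. If half of failures are visual-only, those two figures mean missing 40% and 60% of visible clots on B.

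The reply does not rescue the wording in section 4. Shared 30-minute vital signs are not a shared inspection of the circuit, and a partial clot still has no definition.

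**Conclusion.** The concern holds in a limited form. The statement that the endpoint leaves no room for interpretation does not fit the endpoint as defined, and the open design leans on it. A detection difference is plausible from the protocol's own account of nursing under rinses, and it would favour B and C.

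Its size cannot be derived from the documents. With true failure of 30% on both A and B and 20% of visual-only failures missed on B, the false-positive rate is about 13% at 294 pairs (14% at 350) if half of failures are visual-only, and about 7% if a quarter are. Larger values need assumptions for which the protocol gives no basis. Detection alone is an unlikely source of the whole planned difference between A and C. The point merits a change because the remedy is cheap, not because bias has been shown.

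**What to change.** - In section 4, remove the claim that the endpoint is not open to interpretation. Say instead which limbs are measured and which rest on staff judgement.
- In section 7, state what counts as a partial clot.
- In section 5, require the same inspection of lines and bubble trap in all three techniques, at the existing 30-minute checks and at session end.
- Record which limb (complete, partial, venous pressure) triggered each suspension. Check the pressure limb against the generator's continuous record, but keep the need to suspend as part of the definition. Counting every recorded pressure rise would redefine the endpoint.
- Report complete coagulation, the outcome named in the primary objective, together with pressure-confirmed suspensions as a supportive analysis. This can sit in the statistical analysis plan, and its absence from the protocol is not a fault.

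The cost is slightly more recording at each check. No extra staff are needed, and the pressure data are already captured.

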***Duration of participation***

The duration of participation of each subject will be at least 1 week to 3 months maximum (or 12 triplets).

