**6- Procedures evaluated**

**For all patients :**

- 3 hemodialysis sessions of 4 hours per week

- vascular access : arteriovenous fistula (mono or biponction with 15 G needles) or dual lumen central catheter

- blood flow : 250 to 300 ml / min

- dialysate : flow 500 ml / min, sodium conductivity 14.4 mS / cm ; bicarbonate conductivity 3.3 mS / cm, temperature 36 °C

- Dialysis membrane : AN 69 ST (NEPHRAL 400 ST)

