**Main Analysis**

For the main criteria, 2 analysis will be performed:

- At a treatment group level
- At an individual level

Approximately 60% of included patients will have a temporary contra-indication to systemic heparinisation ranging from 3 to 6 sessions (1 to 2 weeks). These patients will not be analysed individually and will contribute to the global principal analysis.

The global principal analysis will be performed according to 2 approches (MG Kenward and B Jones, The analysis of binary and categorical data from crossover trials, Statistical Methods in Medical Research, 1994 :325-344) :

- a marginal model estimating the effet of treatments taking into account other covariates (order effect or group effect, the Generalized Estimating Equations)
- a subject-specific model using a latent variable taking into account independent responses for a given subject réponses indépendantes pour un sujet. This model is also suited to low numbers of patients.

In the putatively 40% of patients (25 to 30 patients) that may have a prolonged contra-indication to heparin, anb individualized analysis will be performed (after at least 18 sessions to warrant sufficient power). Below 18 sessions, patients will only contribute to the global analysis, as described above.

For the individual analysis, The percentage of technical failures (technique A vs B, and also technique A vs C) will be performed. The exact Fisher test in this setting may be viewed as a randomisation test (ES Edington, Statistics and single case analysis, Progress in behavior modification. Academic Press, Inc. 1984;vol 16 :83-119). Appairment will not be taken into account. This is possible since the dialysis sessions and the efferent judgement criteria are statitically independent. Significativity threshold will be of 10% for a bilateral test, justified by the impoortance given to clinical significance (ES Edington).

At the end of this analysis:

- if one or several techniques are efficient, the patient will end the study
- if no technique apperas superior, the patient may continue the study for at least one triplet of sessions.

To avoid multiple analysis and alpha risk, a new analysis will be performed at 12 weeks, or at the end of the period of contra-indication to heparin. The alpha risk will be of 5% bilaterally.

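### As worded, the technique order is redrawn only every three triplets, so at 18 sessions two orders cannot support Fisher's test as a randomisation test, and technique is partly confounded with position in the week

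*Protocol*

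**What the plan says.** Section 4 (Choice of the experimental plan and justification) randomises each patient to one of six orders of A, B and C. It then adds: "The order of the types of sessions vary all three triplets for the same patient". This applies to patients whose heparin-free sessions go on after the initial period. Section 6 sets "3 hemodialysis sessions of 4 hours per week" for all patients. Section 4 (Duration of participation) gives "at least 1 week to 3 months maximum (or 12 triplets"), so one triplet is one week.

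Section 8 (Main Analysis) plans an individual analysis for the 25 to 30 patients expected to have a prolonged contra-indication: "individualized analysis will be performed (after at least 18 sessions to warrant sufficient power"). It compares A with B and A with C by Fisher's exact test at a two-sided 10% level, and gives as the reason: "The exact Fisher test in this setting may be viewed as a randomisation test". It also states "Appairment will not be taken into account", on the ground that sessions are statistically independent. An order effect is named only for the group-level marginal model.

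**The concern.** A randomisation test takes its validity from the assignments that could have been drawn. Fisher's test treats the 12 sessions of two techniques as freely exchangeable. If one order is drawn and then repeated for three weeks, the sessions are assigned in blocks of nine, and far fewer assignments are possible than Fisher assumes.

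The same rule ties each technique to one slot of the week for three weeks at a time. Any difference between slots then enters the individual comparison, which has no adjustment for position.

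The individual result matters because section 4 justifies the N-of-1 design by the wish to find the best technique for each patient, and section 8 uses the result to decide whether the patient ends the study.

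**Working it through.** **Schedule.** 12 triplets x 3 sessions / 3 per week = 12 weeks, which agrees with the protocol's 3 months. 18 sessions = 6 triplets = 6 sessions per technique. With an order kept for three triplets, that is 6/3 = 2 orders at 18 sessions and 12/3 = 4 at the maximum.

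**Possible assignments at 18 sessions.** Order kept for three triplets: 6^2 = 36 (30 if the second order must differ). New order each triplet: 6^6 = 46,656.

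**Fisher against the actual randomisation.** Suppose A fails 6/6 and B and C fail 0/6.
- Fisher, A v B: 2/C(12,6) = 2/924 = 0.0022.
- Two independent draws: a result as extreme needs A, or B, in the failing slot of both blocks, so p = 2 x (1/3)^2 = 0.22.
- Second order must differ: 2 x 2/30 = 0.13 if the failing slot is the same in both blocks, or 2 x 4/30 = 0.27 if it changes. Both exceed 10%.
- New order each triplet: 2 x (1/3)^6 = 0.0027.

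The Stopping rules paragraph drops a technique after three failures in a row, so 6/6 would not normally be completed. A pattern that respects the rule shows the same gap. Let A fail in weeks 1, 2, 4 and 5 only, and B and C never. Fisher gives 2 x C(6,4)/C(12,4) = 2 x 15/495 = 0.061, which is significant at 10%. Two independent draws still give 2/9 = 0.22. A new order each triplet gives 2 x (1/3)^4 = 0.025.

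**Slot coverage at 18 sessions.** Count the schedules in which at least one technique keeps one slot throughout. One given technique does so in 3 x 2^k of 6^k schedules, where k is the number of orders drawn. All three do so in 6.
- k = 2: 3 x 12 - 3 x 6 + 6 = 24 of 36 = 67%. If the order must change, remove the 6 repeats: 18 of 30 = 60%.
- k = 6: 3 x 192 - 3 x 6 + 6 = 564 of 46,656 = 1.2%.

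With two orders no technique can cover all three slots. A and B share no slot in 18 of 36 schedules (12 of 30 if the order must change).

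**False-positive rate of the individual analysis.** The protocol gives no clotting rate by slot, so the rates below are assumptions. The first three rows average 30%, the protocol's reference rate; 60/20/20% averages 33%. There is no technique effect, sessions are independent, six sessions per technique are completed, and the stopping rule is ignored. With 6 v 6 sessions, Fisher reaches 10% at 4 v 0, 5 v at most 1, and 6 v at most 2 failures. For each schedule,

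P(A-B or A-C significant) = sum over i of P(X_A = i) x [1 - (1 - q_B(i))(1 - q_C(i))],

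where X_A is the number of failures on A, and q_B(i) and q_C(i) are the chances that B's or C's failures differ significantly from i. The result is averaged exactly over all schedules.

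| Assumed clotting by slot | Kept three triplets, order must change | Kept three triplets, order may repeat | New order each triplet |
|---|---|---|---|
| 30/30/30% | 4.4% | 4.4% | 4.4% |
| 40/25/25% | 5.2% | 5.5% | 4.5% |
| 50/20/20% | 7.8% | 9.3% | 5.0% |
| 60/20/20% | 11.8% | 14.6% | 6.3% |

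These are averages over schedules. For the single A-B comparison at 50/20/20%, the worst schedule reaches 13.7%.

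**The case against.** The strongest objection is to the reading. The sentence appears to be a rough translation and may mean that the order changes at every triplet. Its condition, that dialysis continues past the first triplets, fits that sense better, and so does the next statement, that a patient may contribute several sequences. About 60% of patients are expected to have only 3 to 6 sessions; on the literal reading none of them would receive a second order. If a new order each triplet was intended, the problem largely disappears. This stands as a reason for caution. But the rule as worded most naturally describes a different design, and it is the only text in the protocol that says how often the order changes.

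The second objection is that the slot effect is assumed. This also stands. The rationale under the exclusion criteria lists session duration, blood flow, transfusion or parenteral nutrition, and haemoglobin as clotting risks, not position in the week. The larger assumed contrasts (50 v 20%, 60 v 20%) exceed the largest technique contrast planned (30 v 10%), and at 40/25/25% the inflation is under one percentage point or about one. The mismatch between Fisher's test and the randomisation does not depend on any slot effect.

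A reader might infer that technique and weekday are fully confounded in the individual analysis. Confounding is complete within a three-week block, but at 18 sessions it is usually partial: all three techniques keep their slots only if the same order is drawn twice (6 of 36). A reader might also infer that the main group comparison is biased. The six orders are spread across patients and the marginal model allows for an order effect, so the documents do not support that.

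**Conclusion.** The point holds on the literal text. With two orders in 18 sessions, the protocol's reason for using Fisher's test fails: a result that Fisher calls significant can have a randomisation p-value of 0.22. Technique is also partly confounded with position in the week, and one technique or more never leaves its slot in 60-67% of patients analysed at 18 sessions.

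How much this raises false results depends on a slot effect that the documents do not give. It adds nothing with no effect, little at 40/25/25%, and roughly 3 to 4 percentage points at 50/20/20%. Fisher's test is conservative at 6 v 6, so the probability over both comparisons stays below 10% at 50/20/20% and exceeds it at 60/20/20%.

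The consequence is limited to the expected 25 to 30 individually analysed patients. The figures assume a regular weekly schedule; missed sessions, or continuation on two techniques under the stopping rule, would shift the slots. The change is worth making because it is cheap and brings the design into line with the test already chosen.

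**What to change.** In section 4, replace the sentence on how the order varies with: *A new order is drawn at random from the six sequences, independently for every triplet of every patient.*

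The cost is a longer pre-generated list, up to 12 orders per patient, with no extra sessions. If this was already the intent, it only corrects the wording of the randomisation rule. Fisher's test would still ignore the triplets, but in the 6/6 example it would then be close to the actual randomisation (0.0022 against 0.0027).
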